# Translation of two healthy eating and active living support programs for parents of 2–6 year old children: a parallel partially randomised preference trial protocol (the ‘time for healthy habits’ trial)

**DOI:** 10.1186/s12889-020-08526-7

**Published:** 2020-05-07

**Keywords:** Childhood obesity prevention, Fruit, Vegetable, Intervention, Home food environment, Healthy eating, Screen time, Sedentary behaviour, Physical activity, Movement

## Abstract

**Background:**

Parents are key decision makers and role models in establishing and maintaining healthy behaviours in their children. Interventions involving parents have been shown to be more effective than those that do not, but there are barriers to participation. Efficacy trials have previously been conducted on two such parent-focussed healthy eating and active living interventions with the potential to overcome these barriers - *Healthy Habits* (telephone-based) and *Time2bHealthy* (online) with promising results. Further research is now required to determine the effectiveness of these interventions in a real-world context. The *Time for Healthy Habits* study is a 3-arm partially randomised preference trial which aims to evaluate the effectiveness and cost-effectiveness of two theory-based programs to promote healthy eating and appropriate levels of movement behaviours (physical activity, sedentary behaviour and sleep) for parents of 2- to 6-year-old children (*Healthy Habits Plus* telephone-based program and *Time2bHealthy* online program), when compared to a comparison group receiving written materials.

**Methods:**

Participants will be recruited across five Local Health Districts in New South Wales, Australia. The partially randomised preference design initially allows for participants to decide if they wish to be randomised or opt to select their preferred intervention and has been recommended for use to test effectiveness in a real-world setting. Both interventions incorporate multiple behaviour change techniques and support parents to improve their children’s healthy eating, and movement behaviours (physical activity, sedentary behaviour and sleep) and run for 12 weeks, followed by a 3-month and 9-month post-baseline follow-up. Participants will also be asked to complete a process evaluation questionnaire at the completion of the intervention (3-months post-baseline). Outcomes include fruit and vegetable intake (primary outcome), non-core food intake, weight status, physical activity, sedentary behaviour, and sleep habits.

**Discussion:**

To our knowledge, this is the first translational research trial evaluating the effectiveness and cost-effectiveness of a healthy eating and active living intervention in the 2- to 6-years age group. The results will build the evidence base in regard to translation of effective childhood obesity prevention interventions and inform the implementation and delivery of community based childhood obesity prevention programs.

**Trial registration:**

UTN: U1111–1228-9748, ACTRN: 12619000396123p.

## Background

Worldwide, overweight and obesity affects around 23% of children and adolescents in developed countries and 13% in developing countries [1]. The percentage of overweight and obese children and adolescents in Australia is just over one quarter [2]. Appropriate dietary intake, and appropriate levels of movement behaviours (physical activity, sedentary behaviour and sleep) are key factors in early childhood obesity prevention and in establishing habits and routines that are protective against obesity in adulthood [3].

In New South Wales, Australia, a coordinated approach to childhood obesity prevention has focussed on primary and secondary prevention programs delivered at scale in children’s settings as well as community based treatment [4]. Interventions targeting parents as key decision makers and role models in establishing and maintaining healthy behaviours in their children have the potential to complement this approach. Previous studies have demonstrated that childhood obesity interventions targeting parents have been more successful than those which have targeted only children [5–7], and involvement of parents in interventions targeting younger children appears critical [6, 8]. However, there are challenges which make it difficult for parents to become involved in face-to-face programs, such as travel [9], cost [5], childcare for other siblings [10] and finding the time to attend [5]. Online and telephone-based interventions have the potential to overcome some of these barriers, offering potential advantages of convenience and flexibility for parents, and enabling parents to participate regardless of their geographic location.

Efficacy trials have been conducted on two such interventions in preschool aged children: *Healthy Habits* (3–5 years) [11] and *Time2bHealthy* (2–5 years) [12]. *Healthy Habits* is a telephone-based intervention which consisted of 20–30 min telephone counselling calls delivered weekly over 4 weeks. The program was developed by a team of health promotion practitioners, dietitians, psychologists and parenting experts, and is based on the family-based model of intervention proposed by Golan, which draws on socio-ecological theory [13]. The intervention primarily focused on increasing fruit and vegetable consumption. Results from the efficacy trial demonstrated a significant improvement in child intake of fruits and vegetables at 6-month (*p* = 0.021) [14] and 12-month (*p* < 0.01) [15] follow-up. *Time2bHealthy* is an online intervention consisting of six modules delivered over a 3-month period. The intervention was developed by a multi-disciplinary team of health behaviour and parenting experts and practitioners and is guided by Bandura’s Social Cognitive Theory [16]. The efficacy trial found positive outcomes for several nutrition outcomes at the 6-month follow-up, namely a significant reduction in child discretionary food intake (*p* < 0.01), and improvements in nutrition parent self-efficacy (*p* = 0.01) and pressure to eat child feeding practices (*p* = 0.048) [17]. Both *Time2bHealthy* and *Healthy Habits* demonstrated very high levels of user acceptance [17, 18].

Due to promising results from both efficacy trials, this current research aims to build on these previous studies, and examine the effectiveness of the interventions when they are scaled up and adapted for implementation across five Local Health Districts (health jurisdictions) in New South Wales, Australia. Translational research is important to assess population uptake, and the extent to which the effects of the intervention can be replicated when delivered at scale and with more diverse population groups with different sample characteristics and more flexible delivery approaches [19–21]. It is important that the effect of interventions is assessed when delivered in a manner which mimics how they are envisaged to be provided in the community. As such translational intervention methods are likely to be more pragmatic and may be adapted to allow more flexible delivery and less stringent eligibility criteria, instead concentrating on establishing external validity [22]. Fidelity and dosage of an intervention in translational trials may also be lower than efficacy trials as participants may be less likely to adhere to the intervention procedures or there may be less training provided for real-world staff implementing an intervention [23]. Unsurprisingly, when obesity prevention interventions are scaled-up, there is generally a reduction in the intervention’s effect size on outcomes such as weight status, dietary intake, physical activity and sedentary behaviour, possibly due to lower fidelity to original intervention protocols and increased flexibility in delivery [24]. To date, few childhood interventions to promote healthy eating and appropriate levels of movement behaviours (physical activity, sedentary behaviour and sleep) have been translated and evaluated in real-world settings [25] and most of these translational studies have been conducted in school aged-children [26–28] or infants [29]. Studies using a preference trial design (where at least a proportion of the participants have the option of selecting their preferred study arm), have been conducted successfully in different population groups [30–32], but there have been no such studies investigating the effectiveness of a childhood obesity prevention intervention, or any focussing on obesity or obesity-related behaviours in any age group.

The aim of this research study is to examine the relative effectiveness and cost effectiveness of the *Time2bHealthy* and *Healthy Habits Plus* programs when they are applied to existing health services across metropolitan, regional, and rural New South Wales and offered as a free population-wide service across these jurisdictions to mimic real-world implementation.

The primary objectives of the study are to:
Estimate the relative effectiveness of an online behaviour change program (*Time2bHealthy*), a telephone-based support program (*Healthy Habits Plus*) or a written material active control in targeting parents of 2–6 year olds in changing child fruit and vegetable consumption (primary outcome).Estimate the relative effectiveness, cost and cost effectiveness of Time2bHealthy, Healthy Habits Plus and the active control with respect to non-core food consumption, levels of movement behaviours (physical activity, sedentary behaviour (including screen-time), sleep), and weight status effects in accordance with Australian guidelines (secondary outcomes).

The secondary objectives are to:
Explore the most successful approaches to maximise recruitment to these interventions, and the retention of parents within them.Determine the preferred ex-ante and ex-post user delivery medium.

Robust evaluation of the relative incremental effects, costs and cost effectiveness of health promotion strategies in community settings such as Healthy Habits (telephone-based) and Time2bHealthy (online) needs to consider:
(i)at an individual level the a priori relative preferences for and uptake of strategies in target community populations of parents [33–36];(ii)the effects on children and parents exposed to strategies and;(iii)at a community level the community ownership and potential for network and multiplier effects that health promotion programs uniquely enable [37–40].

This study aims to collect trial evidence at an individual level in addressing the first two questions and to facilitate triangulation of evidence in modelling potential of the third.

## Methods

### Study setting

The study is being conducted in New South Wales, Australia and the Local Health Districts of Murrumbidgee, Hunter New England, Illawarra Shoalhaven, Southern New South Wales and South Eastern Sydney are being specifically targeted for recruitment. Together, over 2.6 million people live in these Local Health Districts and they provide a representative sample of young children, with over 300,000 children in the 0–9 years age bracket [41].

### Eligibility criteria

Parents will be eligible if they live in New South Wales, have a child 2–6 years of age at the time of the baseline interview, live with the child at least 4 days on an average week, have access to telephone and internet, and understand and speak English sufficiently to participate. Parents will be excluded if they have previously participated in the *Time2bHealthy* or *Healthy Habits* randomised controlled trials (RCTs).

### Study design

This protocol was written in accordance with the SPIRIT (Standard Protocol Items: Recommendations for Intervention Trials) statement [42]. A three-arm parallel-group randomised preference trial design will be used. The three arms comprise; (1) the *Healthy Habits Plus* telephone-based intervention, (2) the *Time2bHealthy* online intervention, and (3) a comparison arm, which will consist of printed educational material.

To address the question of individuals’ a priori preferences in the target population, as well as the relative effects in children and families, the trial recruitment will initially offer parent participants the option of receiving their preferred delivery medium or be randomised. The preference trial design is particularly well suited to examining the effectiveness of interventions conducted in real-world contexts as it can mimic usual service provision circumstances and allow an estimate of the intervention effects of those who would typically utilise a specific intervention if it was made available. While RCTs are the recognised gold standard for efficacy trials, when the participant has a strong preference in regard to the arm of the study they would choose, they may either be reluctant to be involved if they know they will be randomised, or if they do opt to be involved, they may drop out or not carry out the required activities of the intervention if they are not assigned to their preferred study arm [33–36, 43, 44]. The partially randomised preference trial design allows parents who have a strong preference for the intervention they receive to elect the group to which they are allocated. Parents who do not have a strong preference will be randomly allocated to a group in a 1:1:1 ratio. This study design has been used in previous implementation and translational research [30, 32]. Importantly it can answer the research question regarding which intervention is preferred by parents through the percentage of participants opting to choose each of the interventions.

The study design has a higher likelihood of initial acceptability by participants, if they know that they will be able to choose their preferred study arm, optimising recruitment efforts. Preference allocation can also better reflect real life community preferences and uptake across health promotion strategy alternatives compared with randomising individuals. In a traditional RCT design attempts to randomised individuals can pose recruitment challenges, and population biases with dropout can arise in community settings where participants have a preference for or against a study arm [33–36, 43, 44]. These issues have potential to compromise the generalisability and internal and external validity of individual randomised RCT studies [33, 35, 36]. Despite potential recruitment and retention advantages of preference design over RCTs with randomised individuals, relative effects between arms can be confounded with preference design to the extent there are selection bias between participants who opt to choose alternative intervention arms. To avoid potential for such biases the primary analysis of individual effects for this study will be conducted on participants in the randomised group only (with uptake and secondary analyses being conducted on the entire sample including preference group participants). Stopping rules for the non-randomised preference arm will be applied to ensure enough participants are randomised to power the primary analysis of relative treatment effects.

### Interventions

#### Healthy habits plus

*Healthy Habits Plus* is a telephone-based intervention, which consists of six 20–30 min telephone counselling calls delivered fortnightly over 3 months by trained para-professionals (who have experience in conducting health-related telephone interviews and surveys, but do not necessarily have formal qualifications in a health profession).

The program has been updated for this trial from its original 4-call format focussing exclusively on healthy eating (*Healthy Habits*), to reflect recent guideline updates, and also to incorporate content on movement behaviours (physical activity, screen time and sleep). The program seeks to improve healthy eating, and levels of movement behaviours (physical activity, sedentary screen time and sleep) through modifying: i) the availability and accessibility of foods and beverages, (i.e. ensuring fruit and vegetables are present and stored in a ready-to-eat form), opportunities for physical activity in the home and limiting the presence of screens/devices; ii) supportive family routines (i.e. eating meals without the television, having a set bedtime) and iii) parental role-modelling of health behaviours. Such factors are associated with obesity-related behaviours in young children [45–50].

Consistent with the original intervention and to support behaviour change, the telephone counselling intervention utilises a number of specific behaviour change techniques including barrier identification, goal-setting, self-monitoring, and using prompts or cues [51]. Parents will be mailed print materials (i.e. a guidebook and pad of menu planners) to be used during the telephone contacts and to facilitate action between calls.

To maximise adherence to the intervention, up to 10 attempted calls will be made to participants at each scheduled call, leaving a voice message at the first opportunity. These calls may be complemented by SMS and email as additional measures to contact the participant. After multiple unsuccessful contact attempts, an SMS will sent to ask participants if they would like to continue to participate (Y or N). If they respond ‘N’, they will be withdrawn from the study.

#### Time2bHealthy

*Time2bHealthy* is an online intervention that consists of six modules, each taking approximately 30 min for parents to complete and are delivered over 3 months (i.e. one module every 2 weeks). The program seeks to improve child healthy eating as well as movement behaviours (physical activity, sedentary screen time and sleep), through targeting characteristics of the home environment, developing supportive routines, and encouraging parental modelling of health behaviours. Parents will be required to read content, complete practical activities, watch videos and set goals within each module to facilitate behaviour change. The intervention will incorporate a closed Facebook group (moderated by a health professional) which will allow participants the opportunity to communicate with other members of the intervention cohort (consisting of approximately 15–25 participants per cohort).

To maximise adherence to the intervention, participants will receive an email each week reminding them to log onto the website to complete the modules. One to two moderator posts will be placed in the Facebook group each week reminding participants to log onto the websites and to contribute to the Facebook discussion.

#### Comparison group

The comparison group will receive written educational materials on standard recommendations for healthy eating, and movement behaviours (physical activity, sedentary screen time and sleep). The educational materials, developed by the NSW Office of Preventive Health, also encourage parents to access the *NSW Healthy Kids* and *Raising Children Network* websites. These materials will be supplied to parents at fortnightly intervals over a 3-month period via email or post (based on preference).

### Outcomes

#### Primary outcome

##### Child fruit and vegetable intake patterns

The primary trial outcome is child fruit and vegetable intake patterns, as determined through their score on the fruit and vegetable subscale of the Children’s Dietary Questionnaire (CDQ). The subscale is scored from 0 to 28 with a score of 14 or more recommended based on the Dietary Guidelines for Children and Adolescents [52] and the Australian Guide to Healthy Eating [53].

The questionnaire assesses fruit and vegetable intake patterns over both the past week and 24 h. Acceptable reliability and validity has been established for this questionnaire in assessing child dietary patterns among preschool children at a population level, and for use in assessing the efficacy to improve children’s eating habits [54].

As the CDQ does not assess number of servings, crude servings-based measures of child fruit and vegetable intake will also be used. These questions were taken from the New South Wales Child Health Survey and ask parents *“How many serves of fruit does [child name] usually eat each day?”* and *“How many serves of vegetables does [child name] usually eat each day?”* [55].

This outcome will be assessed by three means: firstly, the absolute change in fruit and vegetable intake will be assessed [55], secondly, the change in scores on the fruit and vegetable subscale of the CDQ [54] will be assessed, and finally, the change in compliance to fruit and vegetable guidelines will be assessed.

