### Study design, sample size and study power

For the primary analysis, sample size calculations for the randomised population are based on detecting between group differences in the proportion of randomised children with fruit and vegetable intake patterns consistent with dietary guidelines, as determined by a score of 14 or more on the fruit and vegetable subscale of the CDQ [54], the primary outcome alone. Accounting for 20% attrition, 117 randomised participants per arm (351 in total) are needed to complete baseline data collection with adequate power, resulting in a sample size of 93 participants per group at the 9-month post- baseline follow-up. For 80% power at a 0.05 significance level, this will allow a 20% detectable difference between intervention and comparison groups in adherence to dietary guideline recommendations assessed using the CDQ fruit and vegetable subscale. The overall sample size of 636 participants was based on a more conservative effect size estimate of 15%.

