### Statistical methods

#### Impact of intervention

All analyses will be conducted using intention-to-treat principles. Generalised estimating equations logistic regression models or mixed models will be used to assess the impact of the intervention on the primary trial outcome of the child fruit and vegetable intake. Secondary outcomes of non-core food intake, weight status, physical activity, sedentary screen time, and sleep will also be assessed. Intervention effects will be compared, firstly for participant level effect including only participants who were randomly allocated and secondly for a community level analysis including all participants adjusting for group (preference) and for other covariates. All significance tests will be 2-tailed with an alpha of 0.05. Post hoc analyses will be conducted to examine interactions by levels of socio-economic status. Exploratory analyses will also be conducted to determine whether preference modifies intervention effects.

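### The protocol defines the primary outcome in different ways and tests everything at 0.05, so no single test decides whether a program worked

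*Protocol article*

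**What the plan says.** Four places in the protocol article bear on this.

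- **Outcomes, Child fruit and vegetable intake patterns.** The opening sentence reads "The primary trial outcome is child fruit and vegetable intake patterns, as determined through their score on the fruit and vegetable subscale", a 0–28 score. The section then brings in serves questions because the CDQ does not count servings, and closes with three means of assessing the outcome: "This outcome will be assessed by three means: firstly, the absolute change in fruit and vegetable intake will be assessed", "secondly, the change in scores on the fruit and vegetable subscale of the CDQ" and "finally, the change in compliance to fruit and vegetable guidelines will be assessed". It gives no order of importance.
- **Participant timeline.** Both the CDQ subscale and the serves questions carry the primary outcome label, in the description of the 3-month assessment.
- **Study design, sample size and study power.** The calculation uses a proportion, "as determined by a score of 14 or more on the fruit and vegetable subscale of the CDQ [54], the primary outcome alone", with 93 per arm at 9 months: "For 80% power at a 0.05 significance level, this will allow a 20% detectable difference between intervention and comparison groups".
- **Statistical methods, Impact of intervention.** Logistic GEE or mixed models may be used for the primary outcome, which leaves binary or continuous open. Then: "All significance tests will be 2-tailed with an alpha of 0.05".

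The trial has two programs and one comparison arm. The Study design section limits the primary analysis of individual effects to randomised participants.

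**The concern.** These sections do not describe the same primary outcome. One names a continuous score, one adds serves and guideline compliance on an equal footing, one gives the primary label to two instruments, and one sizes the trial on a dichotomised score. If the measures disagree at 9 months, for instance if serves improve but the proportion scoring 14 or more does not, the published plan does not say which result decides whether a program worked.

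There are two consequences. The 0.05 attached to each test is not the error rate of the primary conclusion if any of the three may carry it. And the power statement applies to only one of the three. The Discussion says the results will inform large-scale implementation of government-funded programs, so the deciding test should be identifiable beforehand.

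**Working it through.** **Inputs.** From the sample size section: 80% power, two-sided 0.05, a 20-point difference, 20% attrition, 93 completers per arm. From the Outcomes section: three measures. From the Study design section: three arms, allocated 1:1:1. The control-arm rate and the correlations between measures are not stated, so both are varied as assumptions.

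**1. The plan's own figure.** With pooled variance under the null,

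n = [z(0.975)·√(2p̄q̄) + z(0.80)·√(p1q1 + p2q2)]² / (p2 − p1)².

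- 30% v 50%: (1.960 × 0.6928 + 0.8416 × 0.6782)² / 0.04 = 1.9287² / 0.04 = 93.0, so 93 per arm. 50% v 70% gives the same.
- 40% v 60% (the least favourable case): (1.960 × 0.7071 + 0.8416 × 0.6928)² / 0.04 = 96.9, so 97 per arm.
- 93 / 0.8 = 116.25, so 117 per arm; 3 × 117 = 351.

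The figure reproduces. With 93 per arm, power is 78–80% for control rates of 30–50%, and higher at more extreme rates (85% at 20%). This holds for the CDQ 14-or-more form at 0.05 and for no other measure.

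**2. One program against control, three measures at 0.05.**

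- Upper bound under any dependence: 3 × 0.05 = 15%.
- Independent measures: 1 − 0.95³ = 14.3%.

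**3. Both programs against the shared control.** Simulated null trials (1,000,000 draws, three equal arms, normal test statistics, one common correlation among the measures) give the chance of at least one p < 0.05:

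| Correlation | One comparison | Two comparisons |
|---|---|---|
| 0 | 14.2% | 24.8% |
| 0.5 | 12.6% | 21.9% |
| 0.7 | 11.0% | 19.2% |
| 0.8 | 9.8% | 17.3% |
| 0.9 | 8.4% | 14.8% |
| Single measure | 5.0% | 9.0% |

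A more realistic pattern takes compliance to be the dichotomised CDQ score (correlation 0.75–0.8 with the score) and lets serves correlate 0.3–0.7 with the score. This gives 10.8–12.5% for one comparison and 18.9–21.8% for two.

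**4. What the three measures add.** One measure tested for two programs already gives 9.0%. Under the realistic pattern, the three measures raise 5% to about 11–12% per program, and 9% to about 19–22% over both.

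**5. Power if the two comparisons are also adjusted.** At alpha 0.025 (z = 2.241) with 93 per arm:

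- 30% v 50%: Φ[(0.2√93 − 2.241 × 0.6928) / 0.6782] = Φ(0.55) = 71%.
- 40% v 60%: Φ[(0.2√93 − 2.241 × 0.7071) / 0.6928] = Φ(0.50) = 69%.

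**The case against.** The best defence is that a lead measure can be inferred. The sample size section ties the primary analysis to CDQ 14 or more and calls it the primary outcome alone, at 9 months. The Study design section fixes the population. The Outcomes section introduces the serves items as crude additional measures, which reads as supportive. A multiplicity procedure or hierarchy is also commonly left to a statistical analysis plan, which is not shown here, so its absence is no fault.

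Much of this stands. The missing procedure is not the point, and the sample size section does lean towards one measure. It does not settle the matter, because the Outcomes section names the score rather than the cut-off and then lists three means without rank, and the timeline section gives serves the primary label. An analysis plan could resolve this only by overriding published text.

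A reader might go further and infer that assessing the outcome three ways alone produces an error rate of 20% or more. It cannot: three tests at 0.05 are bounded at 15%. About 20% is reached only by pooling both comparisons with control, and in the common-correlation model only at correlations of about 0.65 or less.

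A reader might also count each visit as a separate primary test, giving about 27–39% over the two comparisons, or add the telephone-versus-online contrast and go higher still. The document does not support that count. It repeats the questions at 3 months without making each a separate primary test, it sizes the trial at 9 months, and GEE or mixed models can hold both visits in one analysis.

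**Conclusion.** The concern holds as an inconsistency that must be reconciled: the sections define the primary outcome differently, and all tests share a two-sided 0.05. With no lead measure, the chance of at least one false-positive primary result is about 11–12% per program-versus-control comparison, at most 15%, and roughly 15–25% across the two comparisons.

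The 15% bound needs no assumption beyond three tests at 0.05. The other figures rest on assumed correlations and on counting serves as one test, although fruit and vegetables are asked separately. The inconsistency itself is certain from the text; its size is less so. Whether to adjust across two distinct programs sharing a control is a matter of judgement, and leaving that unadjusted is not an error in this protocol.

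**What to change.** Name one primary variable, at 9 months, in the randomised group, and use the same definition in the Outcomes, Participant timeline, sample size and Statistical methods sections. There are two coherent choices:

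- **CDQ score of 14 or more.** This is the form the sample size rests on, so 93 per arm and about 80% power per comparison stand.
- **CDQ score.** This matches the opening sentence of the Outcomes section, but power must be restated for it. That needs a standard deviation and a target difference, neither of which the article gives.

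Make the other CDQ form, the serves items and all 3-month results secondary, and correct the primary outcome label in the timeline section. State the change in the registry before outcome data are unblinded. All data are still collected; the cost is wording and the loss of primary status for the other measures.

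Keeping all three as primary at 0.05/3 would cost more. On the CDQ 14-or-more form with control rates of 30–50%, it needs 125–130 completers per arm, and 93 gives only 63–66% power.

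Adjusting across the two comparisons with control is optional. If it is adopted, restate power as about 69–71% for a 20-point difference in the CDQ 14-or-more form at alpha 0.025 with 93 per arm.
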